## Abstract

**Background:**

Post-operative pulmonary complications are a significant problem following open upper abdominal surgery. Preliminary evidence suggests that a single pre-operative physiotherapy education and preparatory lung expansion training session alone may prevent respiratory complications more effectively than supervised post-operative breathing and coughing exercises. However, the evidence is inconclusive due to methodological limitations. No well-designed, adequately powered, randomised controlled trial has investigated the effect of pre-operative education and training on post-operative respiratory complications, hospital length of stay, and health-related quality of life following upper abdominal surgery.

**Methods/design:**

The Lung Infection Prevention Post Surgery - Major Abdominal- with Pre-Operative Physiotherapy (LIPPSMAck POP) trial is a pragmatic, investigator-initiated, bi-national, multi-centre, patient- and assessor-blinded, parallel group, randomised controlled trial, powered for superiority. Four hundred and forty-one patients scheduled for elective open upper abdominal surgery at two Australian and one New Zealand hospital will be randomised using concealed allocation to receive either i) an information booklet or ii) an information booklet, plus one additional pre-operative physiotherapy education and training session. The primary outcome is respiratory complication incidence using standardised diagnostic criteria. Secondary outcomes include hospital length of stay and costs, pneumonia diagnosis, intensive care unit readmission and length of stay, days/h to mobilise >1 min and >10 min, and, at 6 weeks post-surgery, patient reported complications, health-related quality of life, and physical capacity.

**Discussion:**

The LIPPSMAck POP trial is a multi-centre randomised controlled trial powered and designed to investigate whether a single pre-operative physiotherapy session prevents post-operative respiratory complications. This trial standardises post-operative assisted ambulation and physiotherapy, measures many known confounders, and includes a post-discharge follow-up of complication rates, functional capacity, and health-related quality of life. This trial is currently recruiting.

**Trial registration:**

Australian New Zealand Clinical Trials Registry number: ACTRN12613000664741, 19 June 2013.

## Background

Elective upper abdominal surgery (UAS) is planned surgery involving an open incision above or extending above the umbilicus [1] and is predominately performed to remove cancerous tissue. Approximately 500 to 1000 procedures per 100,000 head of population are performed annually in developed countries [2, 3]. The most common complication following UAS is a post-operative pulmonary complication (PPC) [4] with a reported incidence of 13–53 % [5–10]. This is higher than the incidence for other major surgical procedures such as open lung resection, cardiac surgery via sternotomy, open lower abdominal surgery, and orthopaedic surgery [11–13]. A PPC is either a specific respiratory complication such as pneumonia or an undefined respiratory dysfunction that is clinically significant, compromises a patient’s predicted recovery, and requires additional medical management [14]. The variability in PPC rates following UAS may be explained by the differing studied patient risk profiles and PPC definitions utilised.

Respiratory pathophysiological changes after UAS are well reported, including atelectasis, impaired mucociliary clearance, diaphragm dysfunction, reduced lung volumes, and respiratory muscle and cough strength deficiencies [15–28]. These can contribute to bacterial proliferation and/or severe atelectasis [17, 29], thus increasing respiratory infection risk [14, 15]. PPCs are associated with increased morbidity, mortality, hospital expenditure, and length of stay (LOS) [5, 30–32]. Strategies to prevent PPCs should remain a high priority [33] due to their relatively high prevalence, relationship to poor patient outcomes, and increased health care costs.

Preventative non-pharmaceutical therapies such as coached deep breathing and coughing (DB&C) exercises and early ambulation are traditionally provided to patients following UAS [34]. Additionally, incentive spirometers [35], positive expiratory pressure (PEP) devices [36], and non-invasive ventilation (NIV) [37] can be utilised. These are often delivered by physiotherapists [8, 38], though in countries where physiotherapists are not involved with this patient group, this type of respiratory therapy is provided by nurses, doctors, or other health professionals [36, 39]. However, the efficacy of post-operative respiratory therapy to prevent PPCs following UAS is controversial. Systematic reviews and meta-analyses have concluded that lung expansion exercises including DB&C [40], incentive spirometry [35], and PEP [41] are of little benefit in reducing PPCs, with only NIV considered efficacious [37, 42]. Specifically, when post-operative ambulation is standardised, the addition of DB&C exercises does not reduce the incidence of PPCs in addition to assisted early ambulation alone [7, 10]. However, almost all clinical trials have included pre-operative physiotherapy (Pre-Op) education and training as usual care delivery to all participants. It is possible that this intervention alone may have independently reduced the risk of a PPC.

Evidence from six clinical trials [43–48] suggests that a single Pre-Op education session may reduce PPC rates by up to 78 % [47, 48] after UAS. However, these trials have methodological limitations, including small sample sizes, inconsistent end points, generalisability restrictions (single-centre trials, predominantly low-risk patient groups), sources of bias (non-random sampling, unblinded assessors and Hawthorne effects), and non-standardisation or reporting of potential confounders. These methodological limitations bring the reported effect on PPC rates with pre-operative physiotherapy education into question.

Even if the reported benefit on PPC rates is a true effect, it is not known if Pre-Op education and training would be effective in the context of recent advances in perioperative management such as Enhanced Recovery After Surgery (ERAS) guidelines. This multimodal package of 10–18 care elements provides significant improvements in complication rates and LOS [49]. Pre-operative education and lung expansion training are strongly recommended within ERAS guidelines, although it is acknowledged that evidence to support this specific element is weak [50]. Additionally, Pre-Op physiotherapy interventions previously studied were predominantly provided the day before surgery. This may not reflect current practice where, in many centres, patients attend a multi-disciplinary assessment clinic one to 6 weeks before their operation [51–53]. It is unknown whether Pre-Op physiotherapy education provided at these longer time intervals might also produce the previously reported effect on PPC prophylaxis.

Surveys of physiotherapy services to UAS patients in Australia have shown a stark reduction in hospitals (20 % down to 5 %) providing Pre-Op physiotherapy over the past 15 years [34, 54]. The reasons for this disinvestment of services are unknown. There are no cost-benefit analysis studies investigating physiotherapy to reduce respiratory complications, so conclusive evidence to inform the allocation of physiotherapy services to pre-operative education and training is lacking. Additionally, only short-term outcomes have been assessed. Reducing PPCs during the acute hospital stay may also improve important patient-focused longer term outcomes such as health-related quality of life (HRQoL) and physical capacity following discharge.

Considering the relative high incidence of PPCs following major UAS and the benefit to both the patient and the health care system if these were reduced, a well-designed, adequately powered trial is needed to determine both the clinical effect and cost benefit that Pre-Op physiotherapy education and training may, or may not, have on reducing PPC incidence following major UAS. Results will guide future cost-effective allocation of services to patients who require UAS.

### Trial objectives

The primary objective of the Lung Infection Prevention Post Surgery - Major Abdominal - with Pre-Operative Physiotherapy (LIPPSMAck POP) trial is to estimate the effect that Pre-Op physiotherapy education and training has on the incidence of PPCs following major UAS, when compared to an information booklet alone. Secondary objectives are to evaluate the effect of Pre-Op physiotherapy on hospital and ICU LOS, hospital costs, incidence of pneumonia, unplanned ICU admissions, time to early ambulation, readiness to discharge from hospital, and, at six weeks following surgery, patient-reported complications, HRQoL, and functional capacity.

## Methods/design

### Trial design

The LIPPSMAck POP trial is a pragmatic, investigator-initiated, bi-national, multi-centre, randomised controlled, parallel group, clinical trial. It is patient- and assessor-blinded, and powered for superiority. Eligible patients will be randomly assigned via concealed allocation to receive 1) a pre-operative assessment by a physiotherapist and provision of an information booklet (control) or 2) a pre-operative assessment, information booklet, plus an additional education and DB&C training session by a physiotherapist (intervention). Post-operative respiratory physiotherapy and assisted early mobilisation will be standardised for both groups. See Fig. 1 for a CONSORT diagram of the LIPPSMAck POP trial and Table 1 for an overview of the trial methods and design.

**Fig. 1 Fig1:**
[figure not shown]
CONSORT flow diagram of the LIPPSMAck POP clinical trial. DB&C deep breathing and coughing, PPC post-operative pulmonary complications, HRQOL health-related quality of life

**Table 1 Tab1:** World Health Organisation (WHO) Trial Registration Data Set for LIPPSMAck POP trial

Data category	Information
Primary registry and trial identifying number	Australian New Zealand Clinical Trials Registry number: ACTRN12613000664741
Date of registration in primary registry	19/6/2013
Secondary identifying numbers	n/a
Trial protocol version	This is Version 4 of the protocol and was enacted on June 2013
Source(s) of monetary or material support	Clifford Craig Medical Research Trust ($60,000 AUD)
	University of Tasmania, virtual Tasmanian Academic Health Precinct ($50,000 AUD)
	Waitemata District Health Board and Three Harbours Health Foundation ($20,000 NZD)
	Tasmanian Health Service - Northern Region ($120,000 AUD)
Primary sponsor	Tasmanian Health Service - Northern Region
Secondary sponsor	Waitemata District Health Board
Contact for public queries	IB, [contact]
Contact for scientific queries	IB, [contact]
Public title	Pre-operative physiotherapy education for the prevention of chest infections following major abdominal surgery
Scientific title	LIPPSMAck POP trial – Pre-operative physiotherapy education for the prevention of post-operative pulmonary complications following major upper abdominal surgery: a bi-national, multi-centre, randomised, double-blinded placebo controlled trial.
Countries of recruitment	Australia, New Zealand
Health condition(s) or problem(s) studied	Pulmonary complications following major upper abdominal surgery
Intervention(s)	Active comparator: Pre-operative physiotherapy education and training
	Placebo comparator: Education booklet
Key inclusion and exclusion criteria	Ages eligible for study: ≥ 18 years
	Sexes eligible for study: both
	Accepts health volunteers: No
	Inclusion criteria: All adults awaiting elective upper abdominal surgery involving an open incision above the umbilicus.
	Exclusion criteria: 1. Any pre-existing condition that would limit ability to participate in the standardised post-operative mobilisation protocol. Defined as any person unable to stand upright and walk for a maximum of 1 min without a seated rest. 2. Unable to understand verbal instructions in English. 3. Unable to attend a pre-admission assessment and education session with a physiotherapist. 4. Open abdominal hernia repairs.
Study type	Type: Investigator initiated, interventional, non-pharmacological, pragmatic, study
	Allocation: Concealed randomisation
	Intervention model: parallel assignment
	Masking: patient and assessor blinded
	Primary purpose: Prevention
	Phase: Phase III
Date of first enrolment	24/6/2013
Target sample size	441
Recruitment status	Recruiting
Primary outcome(s)	Post-operative pulmonary complications during the first 14 days of the hospital stay
Key secondary outcomes	Pneumonia, length of hospital stay, hospital costs, day of ambulation >10mins, length of ICU stay, ICU readmission, post-operative adverse events, day to discharge from post-operative physiotherapy services, patient-reported complications, health-related quality of life, and physical capacity at 6 weeks following discharge from hospital.

### Trial setting

The three participating centres: the Launceston General Hospital (Launceston, Tasmania, Australia), North Shore Hospital (Auckland, New Zealand), and North West Regional Hospital (Burnie, Tasmania, Australia), represent a range of public hospital types. The North West Regional Hospital is a 240-bed rural secondary referral hospital; the Launceston General Hospital is a 330-bed inner-regional, primary referral hospital; and the North Shore Hospital is a 600-bed metropolitan, primary referral hospital. North Shore Hospital has also implemented Enhanced Recovery After Surgery (ERAS) guidelines to all surgical units. All hospitals are government funded, university affiliated, teaching hospitals.

Patients undergoing elective UAS at the participating centres attend an outpatient Pre-Admission Clinic (PAC) session one to six weeks prior to their operation where they are assessed by a multi-disciplinary team consisting of, as a minimum, a registered nurse, anaesthetist, and doctor from the admitting surgical team. Information about the surgical process, pain management, post-operative drips and drains, and expected recovery process are provided as standard care. Whereas, Pre-Op physiotherapy education and training at PAC is not normally provided, post-operative respiratory therapy and assisted ambulation by a physiotherapist are provided as standard care at the participating centres.

Each participating hospital’s institutional review board has approved the trial (the Human Research Ethics Committee (Tasmania) Network, Tasmania, Australia (protocol reference: H0011911), the Health and Disability Ethics Committee, New Zealand (protocol reference: 14/NTA/233)). The trial is conducted in accordance with the Declaration of Helsinki and was prospectively registered on 19 June 2013 at the Australian New Zealand Clinical Trials Registry (http://www.anzctr.org.au): ACTRN12613000664741.

### Eligibility and exclusion criteria

Eligible participants are patients over the age of 18 years attending PAC at the participating centres who are scheduled for UAS expecting to require an abdominal incision longer than 5 cm that will be above, or extending above, the umbilicus (Table 2) and requiring a minimum overnight hospital stay.

**Table 2 Tab2:** List of eligible upper abdominal surgical procedures

Surgical category	Procedure
Colorectal	Anterior resection
	AP resection
	Hartmanns
	Hemicolectomy
	Low anterior resection
	Laparoscopic (+/−hand) assisted colectomy
	Partial colectomy
	Proctocolectomy
	Reversal of Hartmanns
	Sigmoid colectomy
	Small bowel resection
	Subtotal colectomy
	Total colectomy
Upper gastrointestinal	Gastrectomy
	Liver resection
	Oesophagectomy
	Open cholecystectomy
	Open hiatus hernia repair
	Pancreatic surgery
	Whipples
Urology	Adrenalectomy
	Cystic duct excision
	Nephrectomy
	Laparoscopic +/− hand assisted nephrectomy
	Pyeloplasty
	Radical cystectomy +/− ileal conduit
	Radical cystoprostatectomy
Other	Explorative laparotomy
	Splenectomy

Patients are excluded for any of the following criteria: (i) unable to understand verbal instructions in English; (ii) unable to participate in a single pre-admission session with a physiotherapist; (iii) requiring emergency surgery; (iv) a current hospital patient for a separate episode of care; (v) requiring organ transplant; (vi) open abdominal hernia repairs (hernia repairs are generally low-risk procedures which frequently do not involve extensive visceral manipulation and have fewer complications [55]); (vii) being unable to stand upright and ambulate for a maximum of 1 min.

### Randomisation and allocation

An administration assistant independent to the trial will prepare 441 sequentially numbered (1 to 441) opaque envelopes each containing an allocation card wrapped in extra paper or aluminium foil [56]. Allocation sequence is determined by a web-based computer generated (http://www.randomizer.org/) blocked random number table (7 blocks of 63; 1 = intervention, 2 = control). The randomisation tables are then sealed in an opaque envelope, locked within the research institute, and made unavailable to trial personnel. The number of consecutively numbered envelopes provided to each site will be dependent on funding agreements (that is, funded to recruit one block of 63 participants or, on a per patient recruit basis, until the end of the trial).

Local investigators will screen elective surgery and PAC lists daily for eligible patients who will be met face to face by local investigators at their PAC appointment. Informed consent will be obtained from potential participants; each eligible participant will be provided with a trial information sheet which is explained verbally to them and will be invited to participate. Those agreeing will sign a consent form as required by local ethics committees and in accordance with the Declaration of Helsinki. Where the local investigator or eligible patient is unable to attend PAC, the latter will be contacted by telephone and invited to enter the trial. The information and consent form will be mailed by post for signing, and the participant will be requested to bring them to hospital on the day of their operation.

Once informed consent has been obtained and the consent form signed, the pre-operative physiotherapist receives the group allocation for participants by opening the next sequentially numbered sealed opaque envelope containing the randomised group allocation. Patient details will be written on the envelope once opened to ensure that patients are randomised in the same order as recruited and the envelopes filed securely along with the consent form. Potential selection bias will be studied by extracting basic demographic data and planned surgical procedure from all excluded patients’ medical records.

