### Trial interventions

Consenting participants will be randomly assigned to receive either i) a pre-operative assessment from a physiotherapist and provision of an information booklet (control) or ii) an additional education and DB&C training session (intervention).

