### Control group

Participants will have a standardised assessment conducted by a physiotherapist consisting of: questioning on current health co-morbidities, mobility and functional status, smoking history, lung auscultation, subjective assessment of cough quality and strength, sputum production and colour, hand grip strength, Rapid Assessment of Physical Activity (RAPA) [57] and Specific Activity Questionnaire (SAQ) [58] to determine current activity and fitness levels, and Short Form 36 (SF-36 V2) [59] to measure HRQoL (see Data Collection section for further details). Participants will then be provided with an education booklet. This colour booklet contains written and pictorial information about abdominal surgery, expected types of pain management, medical lines and drains, post-operative recovery process, and how to prevent post-operative respiratory complications with early ambulation and self-directed DB&C exercises. The booklet includes detailed written instructions to perform DB&C exercises for two sets of 10 deep breaths followed by three coughs every hour during waking hours. Participants will be instructed to bring the booklet to hospital for reference following the operation. The contents of the booklet will not be discussed with participants in the control group and there will be no additional physiotherapy provided pre-operatively.

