### Intervention group

Intervention group participants will be assessed and provided with an information booklet as per the control group and will then receive an additional single education and training session of approximately 30 min with a physiotherapist. Participants will be given an estimate of their likelihood of a PPC based on a risk prediction tool [5] and educated about the effect of anaesthesia, UAS, and bed rest on mucociliary clearance and lung volumes [19, 20]. To ameliorate these factors and prevent bacteria stagnation [15, 16] the importance of participating in an early post-operative ambulation program and performing self-directed DB&C exercises will be emphasised. Participants will be informed that a physiotherapist will assist them to walk as soon as possible on the first post-operative day, aiming for a duration longer than 10 min and at a pace causing mild breathlessness. Outside these assisted sessions, participants will be advised to walk or exercise by their bedside as frequently as they are able.

As it is frequently not possible to ambulate as early and as often as recommended to assist in preventing respiratory complications [8, 60], participants will be educated on the necessity of performing self-directed breathing exercises to protect their lungs following their operation. They will be instructed to perform DB&C exercises immediately from waking from the anaesthetic and then every hour during daytime waking hours until their first ambulation session, and then at any time when they are not ambulant. The physiotherapist will coach each participant in at least three repetitions, and as many as required to master technique as judged by the physiotherapist. This trial’s DB&C exercises consist of two sets of 10 slow-flow breaths to maximum inspiratory capacity with two to three inspiratory sniff breath stacking manoeuvres [61]. Each breath is held for 3 to 5 s. Each set of 10 breaths is followed by three coughs, or a forced expiratory technique with an open glottis called a ‘huff’, with a small firm pillow pressed over on the abdominal incision to support the wound and to encourage greater expiratory force. Participants will be encouraged to practice these exercises prior to their operation to develop familiarity.

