### Primary outcome

The primary outcome is the development of a PPC within the first 14 post-operative hospital days. PPCs will be diagnosed with the Melbourne Group Scale (MGS) diagnostic scoring tool, which is reliable and valid following UAS and thoracic surgery [5, 8] and has high inter-rater reliability [64]. This tool has eight clinical criteria: four factors relating to symptoms and four to diagnostic markers (Table 5). A PPC will be diagnosed when four or more factors are present from midnight to midnight on one post-operative day.

**Table 5 Tab5:** MGS PPC diagnostic criteria with modifications*

Diagnosis confirmed when four or more of the following are present:
Clinical factors
• New abnormal breath sounds on auscultation different to pre-operative assessment • Production of yellow or green sputum different to pre-operative assessment • Pulse oximetry oxygen saturation (SpO_2_) <90 % on room air on more than one consecutive post-operative day • Raised maximum oral temperature >38 °C more than one consecutive day
Diagnostic factors
• Chest radiograph report of collapse/consolidation. *When a CXR has been taken but no report is available, a ward medical officer or a senior respiratory physiotherapist with more than 10 years’ experience will be asked to report • An unexplained WCC greater than 11 × 10^9^/L • Presence of infection on sputum culture report • Physician’s diagnosis of *pneumonia, URTI, or an undefined chest infection, or prescription of an antibiotic for a respiratory infection

* modification made to original criteria

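### As written, allocation may be known when the pre-operative chest findings are recorded, and those findings are the reference for two of the eight primary-outcome criteria

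*Protocol article*

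**What the plan says.** Four parts of the protocol article bear on this.

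- **Randomisation and allocation.** The only event named before the envelope is opened is consent; once the form is signed, "the pre-operative physiotherapist receives the group allocation for participants by opening the next sequentially numbered sealed opaque envelope". The pre-operative assessment is not mentioned as a preceding step.
- **Trial interventions, Control group, Intervention group.** The assessment is listed among the things that follow assignment: "Consenting participants will be randomly assigned to receive either i) a pre-operative assessment from a physiotherapist". Its content includes "lung auscultation, subjective assessment of cough quality and strength, sputum production and colour". For the other arm the text reads "Intervention group participants will be assessed and provided with an information booklet as per the control group and will then receive" the education and training session. Trial design describes the two arms in the same way.
- **Primary outcome, Table 5.** One criterion is "New abnormal breath sounds on auscultation different to pre-operative assessment". The yellow or green sputum criterion is likewise judged by difference from the pre-operative assessment. A complication is diagnosed when at least four of the eight factors are present on one post-operative day.
- **Blinding.** Clinic staff who know the allocation have no contact with participants after surgery. Post-operative staff, outcome assessors, data analysts and statisticians are blinded. The pre-operative physiotherapist is not on that list.

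**The concern.** An outcome judged as a change from baseline is only as well masked as its baseline. Here the post-operative half of the comparison is masked, but the text does not secure the pre-operative half. Auscultation and the scoring of cough and sputum involve judgement; Pre-operative variables itself calls the cough and sputum scoring subjective.

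If a physiotherapist who knows the arm listens more closely, or records more, in one arm than in the other, the same post-operative sign can count as new in one arm and as unchanged in the other. No bad faith is needed. Only intervention participants are coached through repeated coughing or huffing with that physiotherapist, and nothing in the text closes the baseline record before coaching starts. Sputum first seen during coaching could therefore be entered as a baseline finding in one arm only.

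At stake is the claim that the primary outcome is assessor-blinded. That matters in a trial that presents itself as correcting the unblinded assessment of earlier studies.

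**Working it through.** **Order of steps.** Set side by side, the sections give: consent, then envelope (Randomisation and allocation); assignment, then assessment and booklet (Trial interventions, Control group); membership of the intervention group, then assessment, then training (Intervention group). No section shown places the assessment before the envelope. The order is therefore a reading of several sections together and is not stated in one sentence. The CONSORT diagram and the schedule of events, which might show it, are not reproduced in the text available.

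**How far the reference reaches.** Two of the eight criteria use the pre-operative reference and four are needed. There are C(8,4) = 70 sets of exactly four criteria, of which C(6,4) = 15 contain neither of the two. So 70 − 15 = 55 sets contain at least one. This counts combinations; it is not a probability, because the criteria are not equally frequent.

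**The plan's own sample size.** With 20 % versus 10 %, two-sided alpha 0.05, power 80 %, and pooled variance under the null:

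n per arm = [1.960·√(2·0.15·0.85) + 0.842·√(0.20·0.80 + 0.10·0.90)]² / 0.10² = 198.96, rounded up to 199, or 398 in total.

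This agrees with the stated 398. The point does not affect it.

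**Illustrative size.** The documents give no input for this, so everything that follows is assumption. Let x be the excess share of intervention participants with a recorded baseline abnormality, and h the share of complications that would fall below four factors without that item. If every excess abnormality removed the item, and always in the intervention arm, the apparent risk ratio with no true effect would be 1 − x·h.

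| x | h | share lost (x·h) | apparent risk ratio |
|---|---|---|---|
| 0.05 | 0.3 | 1.5 % | 0.985 |
| 0.05 | 0.6 | 3 % | 0.97 |
| 0.10 | 0.3 | 3 % | 0.97 |
| 0.10 | 0.6 | 6 % | 0.94 |
| 0.20 | 0.3 | 6 % | 0.94 |
| 0.20 | 0.6 | 12 % | 0.88 |

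The false-positive rate follows from a true rate of 20 % in both arms, 199 per arm, and a share s of intervention-arm events lost. Then p₂ = 0.20·(1 − s), d = 0.20 − p₂, and the rejection rate is Φ((d − 1.96·SE₀)/SE₁) + Φ((−d − 1.96·SE₀)/SE₁), where SE₀ uses the pooled rate and SE₁ the separate rates. For s = 0.12: p₂ = 0.176, d = 0.024, SE₀ = 0.03917, SE₁ = 0.03915, giving 0.094.

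| s | two-sided rejection rate |
|---|---|
| 0 | 5.0 % |
| 1.5 % | 5.1 % |
| 3 % | 5.3 % |
| 6 % | 6.0 % |
| 12 % | 9.4 % |

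Five of the six scenarios leave the rate at or below about 6 %. Only the one with both inputs at their maximum goes clearly beyond it.

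**The case against.** The strongest reply is that the order is simply unstated. Consent is a precondition for opening the envelope, and the sections on the arms describe what each arm comprises, not a timetable. The assessment is the same in both arms, so carrying it out does not require knowing the allocation. Two figures are missing and a journal article condenses a fuller protocol. This stands to the extent that the article cannot be cited as proof that sites open the envelope first. It does not remove the point: wherever the text speaks to order, assignment comes first, and no safeguard against that order is given.

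Three stronger readings are tempting, and the documents do not support them.

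- *The unblinded physiotherapist determines two of the criteria.* The baseline sets only a reference. Whether the sign is present after surgery is judged by a blinded assessor, and four factors are needed on one day. A baseline abnormality does not cancel the item, since a finding that differs from it can still count. Sputum colour is recorded with a validated chart. The other six factors use no pre-operative reference.
- *The bias favours the intervention and is material.* Neither its direction nor its size can be derived from the documents. The risk-ratio formula assumes full loss of the item and error in one direction only, so it tends to overstate the effect. Even its worst case, 0.88, is far from the design ratio of 0.10/0.20 = 0.5.
- *The SF-36 and SAQ baselines are exposed in the same way.* These are patient-reported, the patients are described as blinded, and in the intervention arm the education follows the assessment. They are not clinician judgements like auscultation.

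**Conclusion.** The point holds in a limited form. Read as written, the article allows a physiotherapist who knows the allocation to record the partly subjective reference for two of the eight primary-outcome criteria, and the Blinding section does not close that route. The conclusion rests on reading several sections together, with both figures unseen.

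The size and direction of any bias are unknown and it is probably modest. The illustrative rates of 5.1 % to 9.4 % rest entirely on assumed inputs and on all error running one way. The sample size is unaffected. This is worth fixing because the safeguard is cheap, but the trial's validity does not hinge on it.

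**What to change.** In Randomisation and allocation, state that after consent the baseline assessment (at least auscultation, cough and sputum) is completed and locked in the CRF before the envelope is opened. Only the booklet, with or without the education session, is then delivered.

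Telephone sessions need their own sentence, because the article permits enrolment and delivery by telephone and auscultation cannot be done that way. For these, complete and lock the items obtainable by telephone before opening, and have any reference auscultation or sputum finding obtained later recorded by staff unaware of allocation.

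If sites already work in this order, one sentence settles the matter. As recruitment is under way, the order used so far should also be documented.

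The cost is a re-ordering of steps within the visit and a short training note. Coverage remains partial for telephone enrolments, where a masked later assessment may need some arranging. No change to the sample size follows.
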